### Interim analyses and stopping guidelines{21b}

Interim analyses will be performed by an independent statistician after the inclusion of 50 and 100 participants to determine whether the power calculation requires adjustment due to variance differing from initial expectations. No stopping guidelines have been established, as partial wrist denervation is a well-established treatment with a low complication rate [42]. Additionally, patient education and exercise therapy are recommended treatments for OA with minimal risk of adverse events [22].

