### Outcomes {12}

#### Primary outcome measure

The primary outcome is the change of PRWE score [31] with a primary endpoint at 6 months following the start of the intervention. The PRWE is a wrist-specific PROM designed to assess pain and disability in daily activities over the past week. It consists of a pain subscale (5 items) and a function subscale (10 items), with a total score ranging from 0 to 100, where a higher score indicates greater disability. The PRWE is a valid and reliable tool for assessing wrist and hand injuries [32], with strong psychometric properties in wrist OA [33]. The validated Swedish version of the PRWE will be used [34].

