### Implementation {16c}

After obtaining signed informed consent, the dedicated research nurse assigns the randomized envelope to the treating hand surgeon, who is responsible for enrolment and intervention allocation. Participants assigned to surgery are placed on the surgical waiting list by the treating hand surgeon. While the enrolling hand surgeon may perform the procedure, they will have no further contact with the participant to maintain allocation concealment. For participants assigned to patient education and exercise therapy, the hand surgeon will notify the PTs involved in the research study. The designated PTs will then contact the participant to schedule an appointment for the exercise therapy program at the clinic.

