### Composition of the data monitoring committee and its role and reporting structure {21a}

An informal data monitoring committee, composed of designated researchers from the two Departments of Hand Surgery and independent of the study teams, will monitor the data during interim analyses.

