### Adverse event reporting and harms {22}

All adverse events that may be associated with the interventions will be registered. If an adverse event occurs outside of scheduled follow-ups, participants are encouraged to contact their Department of Hand Surgery. If interim analyses reveal a high frequency of unexpected complications, early termination of the study may be considered. Study participants are covered by LÖF.

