### Trial status

This protocol is version 2.0 (19th February 2025). Any future protocol amendments that may impact the study’s conduct or ethics require approval from the ethical review board. Recruitment of participants began in March 2024 and is estimated to be completed in 2027.

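### The variance re-checks are triggered by inclusion of 50 and 100 participants, but the variance they need exists only 6 months after treatment starts

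*Protocol article*

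**What the plan says.** The interim section (21b) fixes the looks by enrolment: "Interim analyses will be performed by an independent statistician after the inclusion of 50 and 100 participants". It gives their purpose as "to determine whether the power calculation requires adjustment due to variance differing from initial expectations".

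The outcome that the power calculation rests on comes later. The primary outcome is the "change of PRWE score [31] with a primary endpoint at 6 months following the start of the intervention", and the Sample size section (14) states its 14-point difference and SD of 24 for that same 6-month point. Treatment does not start at inclusion for everyone. Under Implementation (16c), "Participants assigned to surgery are placed on the surgical waiting list by the treating hand surgeon". The length of that wait is not given. On pace, Trial status says only that "Recruitment of participants began in March 2024 and is estimated to be completed in 2027".

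Three sections bear on what else happens at the looks. The interim section adds that "No stopping guidelines have been established" and gives the low complication rate of denervation as a reason. The section on harms (22) says: "If interim analyses reveal a high frequency of unexpected complications, early termination of the study may be considered". The section on the data monitoring committee (21a) describes an informal committee, independent of the study teams, that "will monitor the data during interim analyses".

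**The concern.** A variance re-check is only as good as the number of outcome values behind it. Counting inclusions fixes the wrong number. When the 50th participant is included, everyone enrolled in roughly the previous 6 months lacks the outcome, and surgery patients who had to wait lack it for longer. The first look would then rest on far fewer than 50 values, with an unplanned imbalance between the arms.

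An SD from so few patients can move a recalculated sample size a long way in either direction by chance alone. Nothing in the text stops a low chance value from shrinking the trial.

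**Working it through.** **Inputs from the protocol article.** Difference 14 points, SD 24, 80% power, p < 0.05, 64 per arm, 140 in total (Sample size); 1:1 allocation (Sequence generation); looks at 50 and 100 inclusions (Interim analyses); outcome 6 months after the start of the intervention (Primary outcome measure); recruitment from March 2024 to some point in 2027 (Trial status).

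**Assumptions, not in the document.** Accrual is even. Recruitment lasts 34 months (to January 2027) to 46 months (to the end of 2027). The wait before surgery is 0 to 3 months, and exercise therapy starts without delay. The test is two-sided. Loss to follow-up is ignored, which favours the plan.

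**1. The plan's own figure.** n per arm = 2 × SD² × (1.960 + 0.842)² / 14² = 0.0801 × SD². With SD 24 this is 46.1, so 47 per arm (47.1, so 48, with the t-test). The stated 64 is not reproduced. That belongs to the Sample size section and is not counted here. I keep SD 24 as the stated expectation.

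**2. Accrual rate.** 140/34 = 4.12 per month; 140/46 = 3.04 per month.

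**3. Participants with a 6-month PRWE at each look** = N − rate × mean lag. The mean lag is 6 months with no wait. With a 3-month wait in the surgery arm only it is (6 + 9)/2 = 7.5 months.

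| Look | No wait | 3-month wait, surgery arm only |
|---|---|---|
| 50 included | 50 − 24.7 = 25 to 50 − 18.3 = 32 | 50 − 30.9 = 19 to 50 − 22.8 = 27 |
| 100 included | 75 to 82 | 69 to 77 |

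So about 19–32 of the first 50 and 69–82 of the first 100 have the outcome.

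**4. Balance at the first look with that wait.** Surgery: 25 − (rate/2) × 9 = 6 to 11. Exercise: 25 − (rate/2) × 6 = 13 to 16.

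**5. Chance variation in the SD.** With a true SD of 24, the 95% range of the observed within-arm SD is 24 × √(χ²/df), where df = completers − 2. The last column is 0.0801 × SD², rounded up.

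| Completers | df | χ² limits | SD range | n per arm at 80% power |
|---|---|---|---|---|
| 25 | 23 | 11.69, 38.08 | 17.1–30.9 | 24–77 |
| 50 | 48 | 30.75, 69.02 | 19.2–28.8 | 30–67 |
| 69 | 67 | 46.26, 91.52 | 19.9–28.1 | 32–64 |

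**6. Is a completer-based trigger feasible?** Enrolled when the 50th participant reaches 6 months: 50 + rate × 6 = 68–75 with no wait, and 50 + rate × 9 = 77–87 if everyone waits 3 months. For the 100th the figures are 118–125 and 127–137. All fall before 140.

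**The case against.** The best defence has four parts.

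- **The wording need not mean the day of the 50th inclusion.** The text says after that inclusion and sets no data cut, and data are cross-checked before interim analyses. This is fair as far as it goes: the cut-off may be set elsewhere. But the article does state a trigger, and it counts inclusions, not outcomes. A look made long enough after the 50th inclusion would be sound, but nothing stated requires that.
- **The second look repairs the first.** This largely stands. With 69–82 completers, the look at 100 already has more outcome data than a first look at 50 completers. It does not undo a revision made after the first look.
- **The gain is moderate.** Moving from 25 to 50 completers narrows the recalculated range from 24–77 to 30–67 per arm. That is a clear gain, but the noise remains, which is why a bar on downward revision matters as much as the timing. That bar is a design recommendation; the text does not contradict it.
- **The magnitudes rest on assumed accrual and waiting time.** True. Even with no wait, however, 18–25 of the first 50 lack the outcome.

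Two stronger readings are tempting. A reader might infer that the trial both rules out and permits stopping at these looks. The interim section denies only preset guidelines, while the section on harms leaves termination to discretion, so both can hold. A reader might also infer unblinded efficacy looks that inflate type I error. The documents do not show this: the stated purpose is variance, the statistician is independent, data analysts are blinded (Who will be blinded, 17a), and the committee is independent of the study teams.

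**Conclusion.** The timing point holds. The stated trigger does not match the stated purpose, and the mismatch is material at the first look: about 19–32 usable outcomes out of 50, and a chance range of about 24–77 per arm with 25 completers. At the second look it is mild. These figures depend on even accrual over 34–46 months and a surgery-arm wait of 0–3 months. The direction does not depend on them, because some of the first 50 will lack the outcome under any steady recruitment.

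On stopping, the finding is one of wording. One section confines the looks to variance and cites few complications as a reason for having no guideline. Another makes complications seen at the same looks a possible ground for ending the trial, without a criterion. The two should be reconciled. No type I error inflation is shown.

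This is an inexpensive improvement worth making. It is not a flaw that invalidates the design.

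**What to change.** Amend the interim section as follows.

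- Trigger the first re-check on 50 participants with an observed 6-month PRWE, and the second on a later fixed number of such participants.
- Use only the pooled SD computed without arm labels. If the true difference is 14, this SD is √(24² + 7²) = 25 instead of 24, or 51 instead of 47 per arm, which is a small error on the safe side.
- Let the sample size stay or rise, but not fall, on the basis of these looks.
- Reconcile the interim section with the section on harms, so that both describe the same purpose for the looks and the same position on early termination for complications.

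The cost is amendment wording and looks that come some months later in recruitment: about 68–75 enrolled at the first look with no wait, and 77–87 if all wait 3 months. Under even accrual the 50th inclusion falls 50/4.12 = 12 to 50/3.04 = 16 months after March 2024, so the first look may already have been made. In that case, apply the new rule to the next one.

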### Methods for additional analyses (e.g. subgroup analyses) {20b}

N/A. No subgroup analyses are planned.

### Methods in analysis to handle protocol non-adherence and any statistical methods to handle missing data {20c}

Missing data will be handled and imputated according to the algorithm outlined by Jakobsen et al. [43].

### Plans to give access to the full protocol, participant-level data, and statistical code {31c}

We plan to give access to the full protocol and statistical code. For information regarding the availability of participant-level data sets, see {29}.

## Oversight and monitoring

### Composition of the coordinating centre and trial steering committee {5d}

The Department of Hand Surgery at Södersjukhuset in Stockholm and the Department of Hand Surgery at Skåne University Hospital in Malmö serve as coordination centres for this study. Both centres are responsible for overseeing and monitoring the study’s progress. The research teams comprise hand surgeons, physiotherapists, a statistician, and research nurses who are affiliated with the hand surgery departments, Karolinska Institutet, and Lund University. The principal investigator ([name]) maintains regular communication with the on-site investigator in Malmö (EB) to oversee the study’s overall coordination and progress. There is no external trial steering committee and no endpoint adjudication committee in this study.

### Composition of the data monitoring committee and its role and reporting structure {21a}

An informal data monitoring committee, composed of designated researchers from the two Departments of Hand Surgery and independent of the study teams, will monitor the data during interim analyses.

### Adverse event reporting and harms {22}

All adverse events that may be associated with the interventions will be registered. If an adverse event occurs outside of scheduled follow-ups, participants are encouraged to contact their Department of Hand Surgery. If interim analyses reveal a high frequency of unexpected complications, early termination of the study may be considered. Study participants are covered by LÖF.

### Frequency and plans for auditing trial conduct {23}

The study teams at both coordination centres will maintain continuous communication throughout the study, discussing enrolment strategies, ethical challenges, and methodological issues. A separate auditing plan is not anticipated to be necessary for the study’s conduct.

### Plans for communicating important protocol amendments to relevant parties (e.g. trial participants and ethical committees) {25}

Significant protocol amendments which may impact on the conduct of the study will only be implemented following approval from the Swedish Ethical Review Authority. The original registration at ClinicalTrials.gov will be updated accordingly.

### Dissemination plans {31a}

The findings of this study will be published in peer-reviewed journals and shared with the participants involved and the scientific community. We also plan to present our results through scientific posters or oral presentations at relevant conferences. Data related to quality improvement of the two interventions will be communicated to healthcare professionals at other Hand Surgery Departments, county hospitals, and patient representative groups.

## Discussion

This study outlines the protocol for an RCT evaluating whether partial wrist denervation results in superior patient-reported outcomes compared to patient education and exercise therapy for individuals with symptomatic wrist OA. To our knowledge, this is the first RCT comparing surgery with a nonsurgical intervention.

Placebo-controlled RCTs are considered the gold standard and provide the highest level of evidence. This trial uses patient education and a self-managed exercise treatment program as the comparator. A systematic review and meta-analysis by Karjalainen et al. [44] suggest that trials with nonsurgical controls (no treatment, usual care, or exercise programs) generate results comparable to those with placebo (sham) controls, supporting the validity of nonsurgical controls in surgical research. Therefore, in this study, we have selected a nonsurgical control as a valid, feasible, and safe alternative to placebo (sham) surgery. Patient education combined with exercise therapy is a core treatment for OA and provides participants with at least the minimum standard of care, making the study ethically sound and clinically relevant. Additionally, using an active treatment comparator rather than sham surgery may increase patient willingness to participate, reducing selection bias. While recruitment rates in placebo-controlled trials are reported to be similar to those in nonsurgical control trials, attrition rates are notably higher in placebo-controlled trials [45]. This suggests that while placebo controls are effective in assessing the efficacy of surgical interventions, they may face challenges related to participant retention. Patient education combined with exercise therapy is a safe intervention with no reported adverse effects, whereas sham surgery introduces unnecessary risks, including scarring, infection, and anaesthesia-related complications. In addition, both partial wrist denervation and exercise therapy aim to preserve wrist motion, improve function, and reduce pain without removing osteoarthritic joint surfaces, allowing further surgical interventions if needed.

PRWE is chosen as the primary outcome since it is a valid and reliable outcome for wrist OA [33] that evaluates both function and pain and focuses on the patient’s perspective [31]. However, PROMs are inherently subjective and may be influenced by age, expectations, socioeconomic status, and psychological factors [46, 47]. To account for this, grip strength and range of wrist motion are included as objective secondary outcomes. Additionally, pain catastrophizing is incorporated as a covariate in the GEE model to adjust for psychological influences on outcomes.

The prevalence of wrist OA is relatively low compared to OA in other joints [48, 49]. By adopting a multicentre design involving two major hand surgery departments in Sweden, this trial has the capacity to recruit a sufficient sample within a reasonable time frame, ensuring statistical power and robust results. Another strength is the focus on two common types of wrist OA, SLAC and SNAC, rather than including a heterogenous group of OA types. This increases internal validity, as treatment outcomes may differ among various OA subtypes.

A potential challenge is treatment adherence in the exercise therapy group. Exercise-based interventions require adherence to the program over weeks or months to achieve benefits, which may be difficult for some individuals [50]. Since pain relief from exercise therapy may take 6–8 weeks [51], maintaining participant engagement is critical. To monitor and evaluate adherence, an exercise diary will be used.

A limitation is the lack of participant blinding due to the nature of the interventions. This introduces a risk of performance bias and detection bias, particularly for subjective outcomes [52]. To strengthen the study design, objective outcomes such as ROM and grip strength are included as secondary outcome measures. Assessors and data analysts will be blinded to minimize bias.

In conclusion, this trial aligns with the “Choosing Wisely” initiative since it includes minimal- and noninvasive treatment options that may lower the risk of low-value care, such as unnecessary and potentially harmful healthcare [53]. If partial wrist denervation proves superior to patient education and exercise therapy, it will provide an attractive surgical option for wrist OA, as it preserves motion, does not require immobilization, has a low complication rate, and is technically less demanding than other surgical salvage procedures. Conversely, if partial wrist denervation is not superior to exercise therapy, it should not be considered for treating wrist OA. Regardless of the findings, this trial will provide critical evidence for guiding and optimizing treatment recommendations for patients with SLAC and SNAC wrist OA (grades 1–3).

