### Objectives {7}

The aim of this study is to compare partial wrist denervation of the AIN and PIN with a nonsurgical treatment that includes patient education and a self-managed exercise therapy program. The primary objective is to investigate whether partial wrist denervation is superior to patient education and self-managed exercise therapy in improving the Patient-Rated Wrist Evaluation (PRWE) score at 6 months following the start of the intervention. Secondary objectives are to evaluate the superiority of partial wrist denervation over patient education and exercise therapy in terms of pain reduction, quality of life, objective functional outcomes, and treatment survival at the 3- and 12-month assessments.

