### Trial design {8}

This is a multicentre, assessor-blinded superiority parallel-group RCT with two treatment arms, adhering to the Standard Protocol Items: Recommendations for Interventional Trials (SPIRIT) [24] and Consolidated Standards of Reporting Trials (CONSORT) guidelines [25]. The overall trial design can be found in the flowchart (Fig. 1) and the SPIRIT diagram (Fig. 2).

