### Sample size {14}

The reported minimal clinically important difference (MCID) of PRWE is 14 points (out of 100) based on previous research [41]. To show a difference of at least 14 points in PRWE score between partial wrist denervation and the education and exercise therapy program (SD 24) [13], after 6 months, 64 participants are required in each treatment arm. The power will be 80% (*p* < 0.05). To account for lost to follow-up, we aim to include 140 participants in total, 70 per treatment arm.

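### A failed superiority test alone cannot support the Discussion's statement against denervation; the confidence interval, read against 14 PRWE points, could

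*Protocol article*

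**What the plan says.** All of this is in the protocol article.

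- Trial design {8}: "This is a multicentre, assessor-blinded superiority parallel-group RCT with two treatment arms".
- Objectives {7}: "The primary objective is to investigate whether partial wrist denervation is superior to patient education and self-managed exercise therapy", measured by PRWE at 6 months.
- Sample size {14}: "The reported minimal clinically important difference (MCID) of PRWE is 14 points (out of 100) based on previous research". With an SD of 24, "64 participants are required in each treatment arm", and "The power will be 80" per cent at p < 0.05.
- Statistical methods {20a}: the same 0.05 threshold for significance.
- Discussion, opening: the question is "whether partial wrist denervation results in superior patient-reported outcomes compared to patient education and exercise therapy".
- Discussion, final paragraph: "Conversely, if partial wrist denervation is not superior to exercise therapy, it should not be considered for treating wrist OA".

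Nothing elsewhere in the article qualifies that last sentence, and the article states no equivalence or non-inferiority margin.

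**The concern.** In a superiority trial judged at p < 0.05, a finding of not superior covers two different results. In one, the data exclude a benefit of the size the protocol calls important. In the other, the data fail to demonstrate a benefit but remain compatible with one of that size. Only the first supports advice against the procedure. The sentence makes no distinction between them.

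It also reaches beyond the comparison tested. The control is an active package of education, a 12-week exercise program and an orthosis, so absence of a difference may mean that both treatments help. The Abstract says surgery may be considered when symptoms persist after first-line care, but the listed eligibility criteria do not require that exercise has failed. A statement about treating wrist OA in general therefore includes patients whom the trial does not specifically study. The same paragraph says the trial will guide treatment recommendations, so an over-strong negative reading could be carried into practice.

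**Working it through.** **Inputs.** From Sample size {14}: target difference and MCID 14 points, SD 24, 64 evaluable per arm, 80% power, 0.05. Assumed: two-sided test (sidedness is not stated), equal SD in both arms, unadjusted comparison of two means, normal approximation for the probabilities. Benefit is counted as positive in favour of denervation.

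**1. From the stated power alone.** Chance of missing a true 14-point benefit = 1 − 0.80 = 20%.

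**2. The plan's own sample size.** n per arm = 2 × (1.960 + 0.842)² × (24/14)² = 2 × 7.85 × 2.94 = 46.1, so 47 (48 with the t-test). The stated 64 does not follow from 14, SD 24 and 80%. It does follow from SD 28: 2 × 7.85 × (28/14)² = 62.8, so 63 (64 with the t-test). That mismatch is a separate matter. The check below is done for both SDs to show that this point does not depend on it.

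**3. Interval and probabilities at 64 per arm.** SE = SD × √(2/64); half-width h = t(126) × SE = 1.979 × SE. A result is non-significant in favour of denervation if the observed benefit is below h. The interval excludes 14 if the observed benefit is below 14 − h.

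| Quantity | SD 24 (stated) | SD 28 (fits 64 at 80%) |
|---|---|---|
| SE | 4.24 | 4.95 |
| h | 8.40 | 9.80 |
| Non-significant, interval still contains 14 | observed 5.60 to 8.40 | observed 4.20 to 9.80 |
| True benefit 14: P(non-significant) = Φ((h − 14)/SE) | Φ(−1.32) = 9.3% | Φ(−0.85) = 19.8% |
| True benefit 14: P(interval below 14) = Φ(−h/SE) | Φ(−1.98) = 2.4% | Φ(−1.98) = 2.4% |
| True benefit 14: P(non-significant and interval contains 14) | 9.3 − 2.4 = about 7% | 19.8 − 2.4 = about 17% |
| True difference 0: P(interval below 14) = Φ((14 − h)/SE) | Φ(1.32) = 91% | Φ(0.85) = 80% |

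Using 1.96 in place of the t quantile gives a half-width of 8.3 and a zone of 5.7 to 8.3 at SD 24, with the same conclusions.

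**4. Example.** At SD 24, an observed benefit of 7 points has the interval 7 ± 8.4, or −1.4 to 15.4. It is non-significant, it does not exclude 14, and the Discussion sentence would still advise against denervation.

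**The case against.** The strongest reply is that this is one sentence of interpretation. It names no p-value, changes no estimand, test or sample size, and can be read as a statement about the true effect. The paragraph also invokes avoidance of low-value care. Preferring the non-invasive core treatment unless surgery is shown to be better is a coherent default, and it needs no proof that the benefit is nil.

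Part of this stands. The sentence is not an analysis rule, and a reader who infers that the protocol contains a formal decision procedure goes further than the text. The value judgement is defensible too, but the sentence does not express it: it states no default and no burden of proof, and goes directly from not superior to a general exclusion. If it is meant as a statement about the true effect, the trial reaches that effect only through an estimate and its interval, which is what the rewording would say.

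Four stronger readings are tempting and are not supported.

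- *The design cannot support any negative conclusion.* It can, through the interval, and probably will if the true difference is near zero.
- *A true 10-point benefit is wrongly rejected in about 35% of trials (SD 24).* Ten points is below the protocol's MCID. In about 15 of those 35 percentage points the interval lies wholly below 14, so a rule based on the interval would reach the same negative conclusion.
- *Precision will be much worse because fewer patients are analysed.* The plan is 64 evaluable from 70 per arm, and nothing in the documents supports a much lower number.
- *The positive conclusion has the same fault.* The article says that superiority would make denervation attractive. It does not equate significance with clinical importance.

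The 20% is also simply the type II error of any trial with 80% power. That is no flaw in the design, but it is the reason a non-significant result should not be read as exclusion of the MCID. A statistical analysis plan that is not shown may contain an interval rule. The point here is what the article states, not that such a rule is absent.

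**Conclusion.** The point holds as a matter of inference and wording. The sentence should be changed, but the design and analysis are not at fault. A non-significant superiority result would miss a true MCID-sized benefit in 20% of trials on the stated power, or about 9% on the stated SD and number per arm. The part that the rewording would correct is narrower: observed benefits of about 5.6 to 8.4 points, which arise in about 7% of trials if the true benefit is 14 (4.2 to 9.8 points and about 17% if the SD is 28). These figures rest on a two-sided 5% level, 64 analysed per arm, a common SD and an unadjusted comparison. Covariate adjustment or a different SD would move them without changing the argument.

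**What to change.** Replace the sentence in the last paragraph of the Discussion with one tied to the 95% confidence interval of the 6-month PRWE difference, along these lines:

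- If the whole interval lies below a 14-point benefit for denervation, conclude that there is no clinically important benefit over education and exercise.
- If the result is non-significant and the interval reaches 14 or more, conclude that superiority was not shown and the result is inconclusive.
- In either case, confine the statement to denervation compared with education and self-managed exercise in the population enrolled.

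If the authors want to favour the non-invasive option when the result is inconclusive, they can say so as an explicit value judgement, separate from the statistical conclusion.

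The cost is about one paragraph. The t-test comparison and the linear GEE model already listed in {20a} both yield such an interval, so no analysis or sample size changes. The article gives 2027 as the estimated end of recruitment, so the wording can be settled before results are known. The downside is that some results will have to be reported as inconclusive.
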